### Subject Replacement

Subjects who are withdrawn during the study will be not be replaced.

### Subject Withdrawal from Investigational Product

Subjects who withdraw from taking the investigational product should be followed-up to monitor safety up until day 28 if possible, i.e. if not previously lost to follow-up.

# INVESTIGATIONAL PRODUCTS & CONCOMITANT MEDICATIONS AND NON-DRUG THERAPIES

## Investigational products

### Study medication and dosages

The study medications (Clinical Trial Material (CTM)) to be evaluated in this study will be prepared and provided by Sigma-Tau i.f.r. S.p.A., Pomezia (Rome), Italy.

The stability of the products used in the study will be determined in advance to assure suitability for use throughout the study. The results of these analyses will be included in the Trial Master File.

#### Drug Dispensing

The study medication will be administered at the clinic or at home by authorized members of the study team (mostly by a study nurse). Study medications given to infants and young children (<2 years old) will be crushed, mixed with 50 ml water, and administered as a slurry if they are unable to swallow. Study medications administered to older children will be given as tablets or fractions of tablets to be taken orally with a glass of water. The study nurse or the investigator will directly observe the intake of study medications. Patients will be observed for one hour to ensure that the medications are not vomited or spat out. Any patient who vomits or otherwise expels the medication within 30 minutes of administration will be retreated with a second dose. If vomiting occurs between 30 and 60 minutes after treatment, only half of the original dose will be given.

#### Dihydroartemisinin-piperaquine (Artekin)

The drug will be given once daily for 3 days.

Dosing schedule

Medications will be administered at the following times:

Day 0: hour “X”

Day 1: hour “X” + 24 hours

Day 2: hour “X” + 48 hours

Dosing table

One tablet of Artekin contains either 20 mg of dihydroartemisinin and 160 mg of piperaquine or 40 mg of dihydroartemisinin and 320 mg of piperaquine. The dosing will be based on bodyweight (assuming a linear relationship between key pharmacokinetic parameters and body weight).

| **Weight in kg** | **mg of dihydroartemisinin to be given daily** | **Dose of dihydroartemisinin as mg/kg/d** |
| --- | --- | --- |
| 4 - 6 | 10 (1/2 tablet with 20 mg) | 1.67 - 2.5 |
| 7 - 12 | 20 (1 tablet with 20 mg) | 1.67 - 2.86 |
| 13 - 23 | 40 (1 tablet with 40 mg) | 1.74 - 3.08 |
| 24 - 35 | 80 (2 tablets with 40 mg) | 2.29 - 3.33 |
| 36 - 75 | 120 (3 tablets with 40 mg) | 1.6 - 3.64 |

| **Weight in kg** | **mg of piperaquine to be given daily** | **Dose of piperaquine as mg/kg/d** |
| --- | --- | --- |
| 4 - 6 | 80 (1/2 tablet with 160 mg) | 13.36 - 20 |
| 7 - 12 | 160 (1 tablet with 160 mg) | 13.36 – 22.88 |
| 13 - 23 | 320 (1 tablet with 320 mg) | 13.92 – 24.64 |
| 24 - 35 | 640 (2 tablets with 320 mg) | 18.32 – 26.4 |
| 36 - 75 | 960 (3 tablets with 320 mg) | 12.8 – 29.12 |

#### Artemether-lumefantrine (Coartem©)

Artemether-lumefantrine (Coartem®, Norvatis Pharma, Basel Switzerland) is co-formulated as fixed-ratio film tablets containing 20 mg artemether and 120 mg lumefantrine. Dosing will follow the recommendations of the manufacturer.

Dosing schedule

Medications will be administered at the following times:

Day 0: hour “X”

Day 0: hour “X” + 8 hours

Day 1: hour “X” + 24 hours

Day 1: hour “X” + 36 hours

Day 2: hour “X” + 48 hours

- 5 - < 15 kg: 1 tablet per dose
- 15 - < 25 kg: 2 tablets per dose
- 25 - < 35 kg: 3 tablets per dose

Tablets will be given, whenever possible with food/drink ~100 ml of reconstituted full cream milk or breast milk as appropriate. In case the infant/child is not able to ingest tablets, the tablet(s) will be dissolved before administration.

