# INTRODUCTION/BACKGROUND

It is generally acknowledged that artemisinin-based combination therapies (ACTs) currently provide the best available treatment option for uncomplicated *P. falciparum* malaria [1]. They give fast therapeutic responses, provide high cure ratios with a short duration of treatment, reduce gametocyte carriage, provide mutual protection against the emergence of resistance, and they are well tolerated. On the north-western border of Thailand, which harbours some of the most multi-drug resistant *P. falciparum* strains in the world, the widespread use of ACTs since 1994 has led to a sustained reduction in the incidence of *P.* *falciparum* malaria, and a hitherto unseen reversal of mefloquine *in vitro* resistance [2]. One of the main obstacles to more widespread adaptation of the use of ACTs in malaria endemic areas has been cost. The two currently available ACTs, artesunate-mefloquine and artemether-lumefantrine, cost USD 3 and USD 2.4, respectively per adult treatment course (expensive for majority of patients or national health services in most endemic countries). Projected costs for other ACTs, which are not yet available, are similar (artesunate-pyronaridine) or even higher (artesunate-atovaquone-proguanil). Furthermore mefloquine is associated with nausea, dizziness, and dysphoria, and has not been adopted in African countries because of high variability in absorption rates, and thus, efficacy concerns in children. Artemether-lumefantrine is very well tolerated but needs to be given twice daily, and lumefantrine has poor oral bioavailability in the if not concurrently taken with fatty food. Chlorproguanil-dapsone-artesunate (CDA) is a possible option that may be relatively inexpensive, but has not yet undergone clinical trials (currently still in phase II). There is also some concern that, by the time CDA is registered, continued widespread use of sulphadoxine-pyrimethamine would have already selected for highly antifolate resistant parasites. Artesunate-amodiaquine is also relatively inexpensive, but is not co-formulated yet, and already has reduced efficacy in Africa because of rapidly emerging parasite resistance to amodiaquine.

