# JUSTIFICATION FOR THIS STUDY

The inexorable spread of resistance of the malaria parasite *P. falciparum* to affordable antimalarial drugs such as chloroquine and sulfadoxine-pyrimethamine causes a public health crisis in sub-Saharan Africa. In the absence of a registered and effective malaria vaccine in the foreseeable future, antimalarial chemotherapy has to be improved dramatically to replace the currently used antimalarials. WHO currently advocates the use of artemisinin-based combination chemotherapy with prompt antiparasitic action and mutual protection against parasite resistance for the treatment of malaria [23, 24]. At present, the only fixed-dose combination registered up to international standards is artemether-lumefantrine (Coartem®), but artemether-lumefantrine has a rather complex treatment regimen requiring a total of six doses administered twice daily over three days, and the price is high (USD 2.4 under special agreements between the manufacturer and WHO). Other fixed-dose artemisinin-based combinations are under development (artesunate-amodiaquine, or chlorproguanil-dapsone-artesunate) but their future use might be compromised by existing cross-resistance to currently used antimalarial drugs (chloroquine and sulfadoxine-pyrimethamine). Dihydroartemisinin-piperaquine is a promising alternative, which has been shown very safe in more than 5,000 treated patients and proved to be highly effective in areas of multi-drug resistance. A fixed-dose co-formulation of dihydroartemisinin-piperaquine (Artekin) is currently developed according to international standards as a once daily 3-day regimen, which is likely to improve adherence and to increase effectiveness. It is comparably inexpensive costing approximately 1 USD per adult treatment. If proved to be safe and efficacious, dihydroartemisinin-piperaquine will be an important addition to the currently available treatment options for uncomplicated childhood malaria due to multidrug-resistant *P. falciparum* in Kenya.

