## Recruitment and trial procedures

The parents or guardians of paediatric patients aged 6-59 months who present to the Pingilikani Health Centre with symptoms suggestive of malaria and a documented, uncomplicated *P. falciparum* infection with an asexual parasite density of 2,000–200,000 parasites/µL, will be informed by the health care facility staff about the ongoing malaria clinical trial. They will be requested to freely consent to let their child participate in the trial. Unwillingness or inability to participate will result in the prescription and administration of the local standard treatment regime for uncomplicated *P. falciparum* malaria (currently 4 mg/kg/day of amodiaquine for 3 days). A screening record will be maintained at the site to log all patients considered as potential subjects into the study, and a recruitment record to log all patients recruited into the study.

The parents or guardians who express interest in participation of their child in the study will receive detailed explanations about the trial from the study staff. Specifically they will be informed that the safety, tolerability and efficacy of two antimalarial drugs will be compared and that their child will be randomly assigned to receive treatment with one of the two drugs (by chance). Finally, they will be asked to sign the informed consent form (see Appendix IV). The study will be explained in the patient’s preferred language (English, Swahili, Giryama), and written informed consent shall be obtained on approved forms (accuracy of translation to be checked by back-translating into English).

At enrolment, children will be assigned a sequential study number. During the first 3 study days (days 0-2) patients will be either be admitted for observation and administration of study medication or managed as outpatients requiring home visits for supervised administration of study drugs at nighttime. Parents/guardians will then be encouraged to return to the clinic for follow up assessments on days 3, 7, 14, 21, 28, 35, 42, 63, and 84 and on any unscheduled day if the child is not well. Compensation for transport to and from the clinic will be provided. All medication will be administered under observation by an authorised member of the study team (physician, clinician, or study nurse).

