### Per Protocol (PP) Population (or Evaluable Population)

Defined as all randomized patients who will be eligible according to the study protocol, received at least 80% of the study medication, will not take other anti-malarial drugs and, in case of the presence of asexual parasite stages on thick or thin blood smears, will have an evaluable PCR analysis.

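### The artemether-lumefantrine dosing list has five times, one short of the six-dose, twice-daily, three-day regimen the protocol describes

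*Protocol*

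**What the plan says.** Protocol section 11.1.1.3 (Artemether-lumefantrine) begins with a general rule, "Dosing will follow the recommendations of the manufacturer", and then sets out when doses are to be given. The list has five entries: hour X on Day 0, "Day 0: hour “X” + 8 hours", "Day 1: hour “X” + 24 hours", "Day 1: hour “X” + 36 hours", and a single Day 2 entry at hour X + 48. The tablets-per-dose weight bands follow directly.

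Two other sections describe the regimen differently. Section 7 (Justification for this study) says the product has a complex schedule "requiring a total of six doses administered twice daily over three days". Section 6 (Introduction/Background) says "Artemether-lumefantrine is very well tolerated but needs to be given twice daily".

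Section 10.5 (Recruitment and trial procedures) provides that during days 0 to 2 children are either admitted or "managed as outpatients requiring home visits for supervised administration of study drugs at nighttime".

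The primary analysis uses the per-protocol population (section 12.3.1). Under section 12.2.2 a child belongs to it only if, among other conditions, the child "received at least 80% of the study medication".

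**The concern.** Days 0 and 1 follow the twice-daily pattern and Day 2 does not. The list is an operative instruction: staff give and observe every dose, so what is written decides what a child receives.

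Three things are at stake.

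- **Treatment.** Children aged 6 to 59 months with falciparum malaria would get an incomplete course in the comparator arm.
- **The primary comparison.** This is a non-inferiority trial with a 5-point margin. If the short course lowers comparator cure, the difference moves in favour of the test drug, and the trial could declare non-inferiority to a weakened reference.
- **Who is analysed.** With no agreed number of doses in a full course, the 80% rule has no fixed denominator in the comparator arm.

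**Working it through.** **Inputs**

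- Described regimen: six doses, twice daily, three days (section 7).
- Listed times: X, X + 8, X + 24, X + 36, X + 48 hours (section 11.1.1.3).
- Tablets per dose: 1 at 5 to under 15 kg, 2 at 15 to under 25 kg; each tablet holds 20 mg artemether and 120 mg lumefantrine (section 11.1.1.3).
- Per-protocol medication threshold: 80% (section 12.2.2).

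**1. The protocol's own count.** Twice daily for three days is 2 × 3 = 6, which agrees with section 7.

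**2. The count from the list.** Day 0: 2. Day 1: 2. Day 2: 1. Total 5, so the six doses are not reproduced.

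**3. Are these lists meant to be complete?** The list for dihydroartemisinin-piperaquine in section 11.1.1.2 has the same layout. Its three times (X, X + 24, X + 48) match its once-daily, three-day description exactly. A complete list is therefore the protocol's own practice.

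**4. Dose received if the list is followed.** 5/6 = 83.3% of the described course.

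| Weight band | Tablets, listed | Tablets, described | Artemether, mg (listed / described) | Lumefantrine, mg (listed / described) |
|---|---|---|---|---|
| 5 to <15 kg | 1 × 5 = 5 | 1 × 6 = 6 | 100 / 120 | 600 / 720 |
| 15 to <25 kg | 2 × 5 = 10 | 2 × 6 = 12 | 200 / 240 | 1,200 / 1,440 |

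**5. The 80% rule.**

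| Doses taken | Share of five | Share of six |
|---|---|---|
| 5 | 100%: meets 80% | 83.3%: meets 80% |
| 4 | 80.0%: meets 80% | 66.7%: does not |

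A five-dose child meets the threshold on either count, so this rule cannot remove under-dosed comparator children from the primary analysis. A four-dose child changes status with the denominator. Against six doses the minimum is 0.8 × 6 = 4.8, that is, five doses.

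**6. Direction of the bias.** Let d be the cure lost in the comparator arm through the missing dose. The estimated difference becomes (test cure) − (reference cure − d) = (true difference) + d. Each percentage point lost by the reference uses up one point of the 5-point margin in the test drug's favour. The documents give no basis for a value of d, so none is assumed.

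**7. The corrected list.** Adding one Day 2 dose gives 2 + 2 + 2 = 6. At the Day 1 spacing of 36 − 24 = 12 hours it falls at X + 48 + 12 = X + 60. That time is inferred; the protocol does not state it.

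**The case against.** The best counter-argument is that the intended regimen can be recovered from the document. Section 11.1.1.3 defers to the manufacturer, and section 7 gives six doses for the registered product. Read together they point to a dropped line rather than a deliberate five-dose course. That is probably right, but it confirms the omission and does not correct it: the manufacturer sentence gives no dose count, and the explicit list that follows it contradicts the intention.

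Other points stand in part:

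- **Night-time visits.** The evening doses already listed on Days 0 and 1 could explain the home visits in section 10.5. That section is compatible with a sixth dose but does not prove one.
- **Text extraction.** A last line lost when the PDF was read cannot be fully excluded. No gap is visible and the neighbouring lines are intact.
- **Withdrawal rules.** Section 10.8.2 makes non-completion of treatment a reason for stopping treatment or excluding a child from further efficacy assessment. It could remove a four-dose child before the 80% rule applies. It depends on the same undefined full course, however: a five-dose child completes the list but not the six-dose regimen. Under section 12.2.1 a withdrawal for non-completion counts as a failure in the modified intention-to-treat analysis, so the ambiguity reaches that population too.
- **The second success condition.** Efficacy also requires a test-arm cure ratio of at least 90%, whatever the comparator achieves. A weakened comparator therefore eases only one of the two conditions. The 90% condition does not check whether the comparator was properly dosed.
- **Oversight.** Operating procedures, fortnightly independent monitoring and the required compatibility of the first 300 patients with the multicentre protocol make literal under-dosing less likely. They do not remove the error from the written instruction.

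**Conclusion.** The concern holds. The comparator list gives five doses where the protocol describes six, and nothing in the document supplies or justifies the difference. Followed as written, children in the comparator arm receive 83.3% of the described course and still satisfy the per-protocol medication threshold.

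The count does not depend on any assumption beyond the list being shown in full. The under-dosing depends on staff following the list literally. The bias in favour of dihydroartemisinin-piperaquine also depends on the lost dose lowering cure, by an amount that cannot be estimated from the documents. Because this is a dosing instruction for young children and also defines the reference treatment of the primary comparison, it must be corrected even if trained staff would probably notice it.

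**What to change.** In section 11.1.1.3, add the second Day 2 dose and state that the course is six doses. Hour X + 60 keeps the Day 1 spacing; confirm it against the manufacturer's recommendations before it is written in.

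State that compliance in the comparator arm is counted against six doses, in the case report form, the Drug Accountability Log and the 80% rule of section 12.2.2, so that at least five of six are needed. In section 10.8.2, say how a child who takes five of six doses is treated under the non-completion reason, so that it does not conflict with the 80% rule.

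The cost is one added line in the schedule, short clarifications of the compliance and completion rules, and a check of the case report form and log, which are not shown and may already be correct. Design, sample size and analysis method are unchanged.

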### Masking of treatment allocation

Because of the clear differences in form and colour of the two drug preparations, blinding of the treatment will not be possible at the point of administration. The use of the double-dummy technique with placebos for dihydroartemisinin-piperaquine and for artemether-lumefantrine would result into the administration of an excessive number of tablets per patient. However, all laboratory analyses including PCR will be performed by staff that will be unaware of the treatment allocation.

### Randomisation

Patients will be randomly assigned to one of the two treatment arms (dihydroartemisinin-piperaquine or artemether-lumefantrine). Blinding in the randomization process will be attained by the use of sealed envelopes. A Standard Operating Procedure (SOP) will control the use of the sealed envelopes.

The randomization list (blocks of 9) will be generated by MDS Pharma Services, using the plan procedure of SAS.

Treatment allocation and administration of medications will be performed by the study nurse or by the investigator at the clinic or during a home visit.

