# DESIGN AND METHODOLOGY

## Study site

The study will be conducted at the new Pingilikani study site, which is being extensively upgraded as an extension of the outpatient department (OPD) clinic at KEMRI Centre for Geographic Medicine Research-Coast (CGMR-C). The Pingilikani study site is located 20 km south of Kilifi town in Kilifi district along the Kenyan coastal region. It lies within the censused area of the Demographic Surveillance System operated by CGMR-C in Kilifi District. Good Clinical Practice will be implemented and adequately monitored. Severely-ill patents requiring hospitalisation can be transferred to Kilifi District Hospital at any times, day and night.

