## Study design

This study is part of a phase III, randomized, open label, two-armed study involving 5 study centres, which will enroll a total 1,500 patients (1,000 dihydroartemisinin-piperaquine; 500 artemether-lumefantrine). Each study will enroll 300 patients into the multicentre study protocol (the other study sites are in Mozambique, Burkina Faso, Uganda, Zambia). In addition, 200 additional patients will be enrolled in the KEMRI study (1) to allow an independent statistical analysis of the KEMRI study and (2) to increase the precision of the estimated chemoprophylactic effect of dihydroartemisinin-piperaquine. Patients enrolled in the KEMRI study will also be followed up for a longer period until day 84 (instead of day 42). These changes will in effect act as an amendment to the multicentre study protocol and will not interfere with the analysis of the multicentre protocol. The data from the first 300 patients (day 0 - day 42) will be fully compatible with the multicentre protocol.

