### Exclusion criteria

1. Participation in any investigational drug study during the previous 30 days.
2. Known hypersensitivity to the study drugs.
3. Severe malaria.
4. Danger signs: not able to drink or breast-feed, vomiting (>twice in 24 hours), recent history of convulsions (>1 in 24h), unconscious state, unable to sit or stand.
5. ECG abnormality that requires urgent management.
6. Presence of intercurrent illness or any condition which in the judgment of the investigator would place the subject at undue risk or interfere with the results of the study.
7. Severe malnutrition (defined as weight for height <70% of the median NCHS/WHO reference).

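### One fixed block size of 9, printed in the protocol of an open-label, single-site study, means that sealed envelopes cannot guarantee allocation concealment

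*Protocol*

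**What the plan says.** Protocol section 11.1.3 (Randomisation) gives one block size and no other: "The randomization list (blocks of 9) will be generated by MDS Pharma Services, using the plan procedure of SAS". The same section rests concealment on envelopes, "Blinding in the randomization process will be attained by the use of sealed envelopes", with a standard operating procedure (SOP) governing their use. It also says who acts at the moment of allocation: "Treatment allocation and administration of medications will be performed by the study nurse or by the investigator".

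The setting is described elsewhere:

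- Section 10.2 (Study design): "This study is part of a phase III, randomized, open label, two-armed study involving 5 study centres".
- Section 11.1.2 (Masking of treatment allocation): because the two products look different, "blinding of the treatment will not be possible at the point of administration". Laboratory staff, including those doing PCR, are kept unaware of the arm.
- Section 10.1 (Study site): "The study will be conducted at the new Pingilikani study site". This is one of the five centres of the wider trial.
- Section 10.5 (Recruitment and trial procedures): study numbers are sequential, and records of screened and recruited patients are kept.
- Section 11.1.5 (Accountability procedures): the site keeps a drug log by subject number, date and number of tablets.

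The block's composition is not printed. The multicentre totals in section 10.2, "1,000 dihydroartemisinin-piperaquine; 500 artemether-lumefantrine", imply 6:3. Section 10.4.2 (Sample size calculation) plans 250 per group, to which the nearest split of 9 is 5:4.

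**The concern.** An envelope hides an allocation only if the allocation cannot be worked out from those already opened. Here one team sees one series of visibly different treatments, in numbered order, with a drug log as a written record. The block size is fixed and appears in a document that the team holds. Once one arm's places in a block are used up, every remaining place in that block is determined.

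Foreknowledge matters when entry involves judgement. Exclusion criterion 6 covers "any condition which in the judgment of the investigator would place the subject at undue risk or interfere with the results of the study", and inclusion criterion 6 depends on the parents' willingness and ability to comply. A child could be enrolled, deferred or excluded with the next assignment in mind. That selection happens before any outcome is measured, so blinded microscopy and PCR cannot correct it. The primary comparison is non-inferiority with a 5-point margin, so a modest prognostic difference between arms would count.

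**Working it through.** The protocol gives no predictability figure, so there is none to reproduce.

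**Inputs.** Block size 9 (section 11.1.3); 500 children at Kilifi (section 10.4.2); composition 6:3 (from section 10.2) or 5:4 (nearest to section 10.4.2). Both are carried through because the protocol does not settle which applies.

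**Allocations determined per block.** In a block with *a* places in one arm and *b* in the other, a given place of the first arm comes after all *b* of the second with probability 1/(b+1). The expected number of determined places is therefore

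a/(b+1) + b/(a+1).

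- 6:3: 6/4 + 3/7 = 1.50 + 0.43 = 1.93 of 9, or 21.4%.
- 5:4: 5/5 + 4/6 = 1.00 + 0.67 = 1.67 of 9, or 18.5%.

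Listing every ordering (84 for 6:3, 126 for 5:4) gives the same values. The last place of a complete block is always determined. The last two or more are determined in 50% of 6:3 blocks and 44% of 5:4 blocks.

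**Children affected.** 500 = 55 × 9 + 5, which is 55 complete blocks and 5 places of a further one.

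- 6:3: 55 × 1.929 = 106.1, plus about 0.06 from the partial block: about 106.
- 5:4: 55 × 1.667 = 91.7, plus less than 0.01: about 92.

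Applying 21.4% and 18.5% directly to 500 gives 107 and 93. That is slightly high, because almost nothing is determined in the incomplete block. If the first 300 and the further 200 had separate lists, the complete blocks would still number 33 + 22 = 55.

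**Guessing.** The best strategy names the arm with more places left in the block.

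| Split | Best guess correct | Always naming the larger arm | Gain |
|---|---|---|---|
| 6:3 | 72.8% | 6/9 = 66.7% | about 6 points |
| 5:4 | 67.0% | 5/9 = 55.6% | about 11 points |

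**Scale against the margin (an assumption, not an estimate).** Under 6:3, 1.5 of the 6 dihydroartemisinin-piperaquine places in a block are determined, which is 25% of that arm. If all of these went to children whose chance of cure was 5 points higher, the arm's cure ratio would rise by 0.25 × 5 = 1.25 points, a quarter of the margin. Nothing in the protocol says that this would happen, or in which direction.

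**Effect of varying the block size.** This was simulated at 2:1 for series of 500, with an observer who knows the full history and the set of possible sizes but not the block boundaries. The share of allocations known with certainty was:

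- fixed size 9: 21.3%
- sizes 3, 6, 9: 3.9%
- sizes 6, 9, 12: 2.2%
- sizes 9, 12, 15: 1.5%

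The 1:1 case was not simulated.

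**The case against.** The strongest reply is that deduction needs more than the printed size. Staff must keep a tally, know where blocks begin and know the composition, which the protocol does not print and on which its sections point to different ratios. Even then about four fifths of allocations are not determined, and under 6:3 the gain from best guessing is only about 6 points. All of this stands. A reader might infer that a fifth of assignments are simply known before the envelope is opened and that concealment fails altogether. The protocol does not support that: it supports deducibility under stated conditions, for part of the sequence.

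The protocol also has safeguards: the envelope SOP, consent before any eligibility testing, records of screened and recruited patients, and fortnightly independent monitoring. Age, weight and parasite density limits are objective. Dosing is observed, so expected adherence to treatment gives little to steer by. These points narrow the route and make selective exclusion easier to detect afterwards. They do not stop a closing allocation being deduced, because controlling when an envelope is opened does not hide what earlier envelopes have revealed. Composition can be inferred after a few complete blocks.

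A further objection is that this level of detail may sit in the SOP or in a statistical analysis plan, neither of which is shown. That would answer a complaint of omission. Here the protocol itself fixes and discloses the size.

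**Conclusion.** The point holds as a limited weakness in design: with a single disclosed block size in this setting, concealment cannot be guaranteed. About a fifth of allocations could be deduced in advance, about 106 of 500 under 6:3 or about 92 of 500 under 5:4. This assumes that staff tally assignments in order within one series per list and infer the composition. The conclusion does not depend on which split applies. No steering is alleged, and the size and direction of any bias cannot be derived from the protocol. It calls for a cheap improvement before enrolment and does not invalidate the comparison.

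**What to change.** Before enrolment, have the contract research organisation generate the list with randomly varying block sizes. First reconcile the allocation ratio across sections 10.2, 10.4.2 and 11.1.3, since blocks of 9 cannot give 250 per group. Each size should then be a multiple that fits the settled ratio. Remove the parenthesis giving the block size from section 11.1.3, say only that permuted blocks of varying size are used, and hold the sizes in a restricted randomisation document that site staff cannot see. Deleting the number while keeping blocks of 9 would not be enough, because the size has already been disclosed. When the envelope may be opened is best checked against the SOP, which may already cover it.

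The work is one re-run of the list program and one line of protocol text. The downsides are a possible imbalance of a few patients between arms and the need to coordinate with the multicentre scheme, because section 10.2 requires the data from the first 300 patients to remain compatible with it.
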